|                 | 
ordinal data (discrete data) number, median, interquartile range and extremes will be calculated. If found suitable, ordinal data will be considered as supplementary metric data. For all nominal data the frequency distribution will be presented in frequency tables. The values of metric data can be merged in ordinal classes according to clinical criteria to determine their frequency distribution. Explorative estimation for the structural consistency of the groups regarded will be proved by a descriptive comparison of demographic data, values at screening and secondary (further) endpoints.
 
At the current stage of knowledge, no reliable information about the underlying scientific object of research (assessments of common cold symptoms) is available. Therefore, no statistical planning of sample size is possible and the number of 200 subjects is only determined by practical needs of the investigator, taking account for the inter- and intra-individual variability and underlying physiological processes.
 |
| GCP conformity: | 
This clinical investigation will be performed based on the principles of the ICH GCP E6 (R2) and ISO 14155.
                                                                                                                                                                                                                                                                                                                                                                                                                                                                                                                                                                                                                                                                                                                                                                                                                                                                                                                                                |

### 3 LIST OF TERMS AND ABBREVIATIONS

|       |                                                                                                            |
|-------|------------------------------------------------------------------------------------------------------------|
| AE    | Adverse Event                                                                                              |
| ADE   | Adverse Device Effect                                                                                      |
| BMI   | Body Mass Index                                                                                            |
| BfArM | Federal Institute for Drugs and Medical Devices
("Bundesinstitut für Arzneimittel und Medizinprodukte") |
| CA    | Competent Authority                                                                                        |
| CHMP  | Committee for Medicinal Products for Human Use                                                             |
| CIP   | Clinical Investigation Plan                                                                                |
| CRA   | Clinical Research Associate                                                                                |
| CRF   | Case Report Form                                                                                           |
| CRO   | Contract Research Organization                                                                             |
| EC    | Ethics Committee                                                                                           |
| FAS   | Full Analysis Set                                                                                          |
| FSFV  | First subject first visit                                                                                  |
| GCP   | Good Clinical Practice                                                                                     |
| GI    | Gastrointestinal                                                                                           |
| ICH   | International Conference on Harmonization                                                                  |
| ICF   | Informed Consent Form                                                                                      |
| IP    | Investigational Product                                                                                    |
| ISF   | Investigator Site File                                                                                     |
| ITT   | Intention To Treat                                                                                         |
| LSO   | Last Subject Out                                                                                           |
| MPG   | German Act on Medical Devices
("Medizinproduktegesetz")                                                 |
| MPSV  | Ordinance on Medical Devices Vigilance
("Medizinprodukte-Sicherheitsplanverordnung")                    |
| PP    | Per Protocol                                                                                               |
| SAE   | Serious Adverse Event                                                                                      |
| SADE  | Serious Adverse Device Effect                                                                              |
| SAP   | Statistical Analysis Plan                                                                                  |
| SOP   | Standard Operating Procedure                                                                               |
| TMF   | Trial Master File                                                                                          |
| USADE | Unexpected Serious Adverse Device Effect                                                                   |
| V     | Visit                                                                                                      |
| VCAS  | Valid Case Analysis Set                                                                                    |
| WHO   | World Health Organization                                                                                  |

All official and professional titles and any references to persons in this document apply to both genders.

## 4 INTRODUCTION

A common cold is a trivial catarrhal infection of the upper respiratory tract (Tyrrell 1996). Acute respiratory diseases are among the most frequent illnesses at all. They are almost exclusively based on viral infections and mostly show an epidemic progression affecting all age groups, with the well-known autumn/winter peak (Glathe 1992, Wagner 1996).

The typical progression may differ in individual subjects, but in any case it presents a burden for the subject. Most commonly, adult subjects complain of a general feeling of sickness, headache, pain in the limbs, rhinorrhea (runny nose), sore throat and difficulty swallowing, hoarseness, coughing and altered quality of sleep.

An adequate and practice relevant, primary causal (e.g. antiviral) therapy against a trivial acute infection of the upper respiratory tract is currently not available. However, many of the complaints can be reduced by treating the symptoms (Ziegler 1995).

The development of effective treatment options is difficult due to the multiple virus types and the ways of interaction between virus and host (Johnston, 1997; Hendley, 2008). Numerous remedies are available on prescription and over the counter, yet there is still no reliable treatment and the potential side effects may be substantial (Eccles et al., 2010). Effective solutions with minimal side effects (given the nonhazardous nature of the disorder) are required.

CMS016317 is ColdZyme® Mouth Spray (Enzymatica AB, Sweden), a marketed Class I medical device, with the following composition: glycerol, water, cod trypsin, ethanol (<1 %), calcium chloride, trometamol and menthol. It is to be used when exposed to cold viruses or early on when cold symptoms occur. It works by coating the lining of the mucous membrane, creating a protective barrier. The barrier acts osmotically on the cold viruses, trapping them and preventing them from binding with human cells, helping the body to remove them naturally.

The present exploratory study is designed to evaluate the use of various assessments of common cold symptoms for proof of efficacy of CMS016317.

## 5 DESCRIPTION OF THE INVESTIGATIONAL PRODUCT

CMS016317 is ColdZyme® Mouth Spray, a medical device classified as a Class I device (CE-marked and marketed since 2013) under Council Directive 93/42/EEC on Medical Device and MED-DEV Guidance Document 2.4/1. Rev 8, June 2010, with the following composition: glycerol, water, cod trypsin, ethanol (<1 %), calcium chloride, trometamol and menthol. The manufacturer of ColdZyme® Mouth Spray is Enzymatica AB, the study sponsor.

ColdZyme® Mouth Spray is to be used when exposed to cold viruses or early on when cold symptoms occur. It targets the mouth and throat, where cold viruses take hold and multiply.

The intended use of ColdZyme® Mouth Spray (according to the Instruction for Use, 2016):

- It reduces the probability of catching a cold
- it can help shorten the duration of a cold if used at an early stage of the infection.

In a recent non-clinical study (Stefansson et al, 2017), it was demonstrated that ColdZyme® Mouth Spray has a virus deactivating ability against four major common cold viruses. A virucidal efficacy suspension test was conducted using ColdZyme® Mouth Spray against each of the challenge viruses in suspension. ColdZyme® Mouth Spray deactivated rhinovirus type 1A by 91.7% (1.08 log10), rhinovirus type 42 by 92.8% (1.14 log10), human influenza A virus H3N2 by 96.9% (1.51 log10), respiratory syncytial virus (RSV) by 99.9% (2.94 log10) and adenovirus type 2 by 64.5% (0.45 log10).

Further, a recent clinical study (Clarsund et al., 2017) investigated the performance of ColdZyme® Mouth Spray in rhinovirus-inoculated healthy volunteers. This randomized, doubleblind, placebo-controlled pilot study was conducted on 46 healthy volunteers inoculated with rhinovirus 16 via the nose. Subjects self-administered ColdZyme or placebo 6 times daily for 11 days. Symptoms were recorded daily in a diary. Rhinovirus 16 in nasal and oropharyngeal samples at days 0, 3, 4, 6, 7 and 10 were quantified by RT-qPCR. The primary outcome measure was the reduction in viral load in oropharyngeal samples. Exploratory analysis measuring the total viral load (i.e., area under the curve) for days 3 - 10 in successfully inoculated subjects found that ColdZyme® Mouth Spray treatment resulted in a lower total viral load in the oropharynx ( $p = 0.023$ ). In subjects who experienced symptomatic common cold, treatment with ColdZyme® Mouth Spray resulted in a reduction in the number of days with common cold symptoms from 6.5 to 3.0 days ( $p = 0.014$ ) in comparison to placebo.

## **6 RISK ASSESSMENT FOR THE INVESTIGATIONAL PRODUCT AND THE CLINICAL INVESTIGATION**

### **6.1 PROSPECTIVE CLINICAL BENEFIT**

Based on the available clinical evidence, an improvement of the common cold symptoms is anticipated within the period of treatment with CMS016317 (ColdZyme® Mouth Spray).

### **6.2 ANTICIPATED ADVERSE DEVICE EFFECTS**

The essential requirements relevant for the device safety and performance have been assessed within an extensive risk management process, which incorporates biological evaluation, design, usability, production, quality and regulatory processes and clinical validation. Evaluation of the analysis combining all potential risks has concluded that the ColdZyme® Mouth Spray is free from unacceptable risk. No contraindications for use of the device, other than hypersensitivity to any of the ingredients, have been identified in the risk management process. Risks have been further addressed in post market surveillance and in post market investigations. No new or unacceptable risks have been recorded, and no adverse events related to the use of the ColdZyme® Mouth Spray have been reported during post market investigations. Trypsin is also Generally Regarded As Safe (GRAS) in humans by the US FDA (21 CFR 184, §184.1914).

Therefore, the device is concluded to achieve its intended purpose and fulfil essential requirements regarding safety and performance.

ColdZyme® Mouth Spray should not be used by individuals hypersensitive/allergic to any of the ingredients. Further, it should not be used continuously for more than 30 days, as there is no clinical information available about long-term use.

It is most important not to inhale when applying the spray since this may cause transient asthma-like symptoms, such as coughing and hoarseness; the study subjects will be instructed accordingly.

### **6.3 RISK ANALYSIS**

#### **6.3.1 Product Specific Risks**

Safety of ColdZyme® Mouth Spray has been assessed within the risk management process and evaluation of the analysis combining all potential risks has concluded that ColdZyme® Mouth Spray does not impose any unacceptable risk. The essential requirements relevant for ColdZyme® Mouth Spray safety have been handled according to the Risk Management process. Risks have been identified, evaluated according to the essential requirements with applicable harmonized standards, mitigated and, where applicable, controlled via verified control measures.

#### **6.3.2 Risks due to Manufacturing Errors**

To mitigate the risk, the production is monitored by means of a quality management system ensuring that the quality of the manufactured product complies with the specified standards.

### **6.3.3 Risks due to Overdose**

To mitigate the risk, the dosing recommendations for the intended use of the device are derived from the clinical evaluation of the product.

### **6.3.4 Risks due to Improper Use**

There is labeling on the device packaging to state proper use and general and specific precautions including 'use by date' statement and proper storage requirements. In the study, the subjects will be trained on proper use (please refer to section 10.2).

### **6.3.5 Risks due to Interactions with Pharmaceutical Products and/or Contraindications**

According to the Instruction for Use (2016), ColdZyme® Mouth Spray should not be used by individuals hypersensitive/allergic to any of the ingredients.

### **6.3.6 Overall risk Assessment**

According to the Risk Management Report, possible risks are acceptable due to low probability of occurrence and existence of sufficient countermeasures.

## **6.4 RISKS ASSOCIATED WITH PARTICIPATION IN THE CLINICAL INVESTIGATION**

All clinical assessments are standard in health care applied for upper respiratory tract infections.

## **6.5 RISK-TO-BENEFIT RATIO**

The current overall risk assessment reveals that, when used as intended, CMS016317 (ColdZyme® Mouth Spray) does not pose an unjustifiable risk. Given the fact that the evidence available suggests beneficial effects with respect to the common cold symptoms, the risk-to-benefit-ratio in the present investigation may be considered as favourable.

## 7 OBJECTIVES OF THE CLINICAL INVESTIGATION

The main goal of this single (investigator)-blind, randomized, parallel-group design, pilot clinical investigation is to evaluate the use of various assessments of common cold symptoms for proof of efficacy of CMS016317.

### 7.1 EFFICACY PARAMETERS

Main endpoints:

Evaluation of various assessments of common cold symptoms by the observed magnitude of treatment effects:

- Sore Throat Scale
- Irritated Throat Scale
- Jackson scale – total score, local symptoms, systemic symptoms, 2-item score (sore throat & malaise)
- WURSS-21 QoL subscore
- Percentage of subjects with prevention of cold outburst

Further endpoints [SEP]

- Duration of common cold symptoms
- Use of concomitant treatment / remedies
- Global evaluation of efficacy by subjects at study end

### 7.2 SAFETY PARAMETERS

- Physical examination
- Blood pressure
- Pulse rate
- Global evaluation of safety and tolerability by subjects at study end
- Assessment of adverse events throughout the study
- Assessment of device deficiency at V2 and V3

### 7.3 FURTHER PARAMETERS

- Assessment of IP usage (based on IP account) in verum group

## 8 DESIGN AND DURATION OF THE CLINICAL INVESTIGATION

### 8.1 DESIGN OF THE CLINICAL INVESTIGATION

The present clinical investigation is a single (investigator)-blind, randomized, parallel-group design, pilot study.

| Screening/
enrolment | Treatment start      | Control visit                                   | Treatment
stop                             |
|-------------------------|----------------------|-------------------------------------------------|-----------------------------------------------|
| All                     | Onset
of symptoms |                                                 |                                               |
| Visit 1                 |                      | 2
Within 3 days
from start of
symptoms | 3
16+/-4 days
from start of
symptoms |

Figure 1: Visit schedule

### 8.2 DURATION OF THE STUDY

The study duration for each subject is maximally 16 weeks.

The expected start date of this study is Q1 2018. The clinical phase of the study is expected to be completed by Q1 2019.

If the required number of subjects with cold symptoms would not be achieved in the winter season 2017/2018, the recruitment would be stopped between March and September 2018 and continued in the next winter season (2018/2019).

## 9 SELECTION OF STUDY SUBJECTS

### 9.1 NUMBER OF SUBJECTS

A total number of expectedly 300 subjects will be enrolled in the study as eligible study participants and randomised at V1. Thereof, the first 200 who attend the V2 should complete the study (i.e. enter the treatment phase upon experiencing symptoms).

Depending on the percentage of subjects from those randomized at V1 who actually develop symptoms during the study period, the envisaged number of 300 recruited subjects may deviate from the final number of subjects needed.

For reasons of practicability/logistics of recruitment, the targeted number of 200 subjects with symptoms may be subject to deviations of maximally +/- 20 subjects.

### 9.2 INCLUSION CRITERIA

1. Men and women
2. Age 18 to 70 years old
3. Increased risk for common cold (at least 3 self-reported occurrences of common cold within the last 12 months prior to V1) but generally in good health
4. Readiness to comply with trial procedures:
  - Use of IP as recommended (verum group)
  - Filling in diary
  - Keeping habitual diet and physical activity level
5. Women of child-bearing potential:
  - Have to agree to use appropriate contraception methods
  - Negative pregnancy testing (beta human chorionic gonadotropin test in urine) at V1

Participation is based upon written informed consent by the participant following written and oral information by the investigator regarding nature, purpose, consequences and possible risks of the clinical study.

### 9.3 CRITERIA FOR CONTINUATION AT V2

Subjects having Visit 2 within maximally 3 days after onset of common cold symptoms according to predefined criteria for required symptoms, and, for verum group, start of IP use, will continue study participation.

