### **12.2 VISIT 2 (V2), 1– 3 DAYS AFTER SYMPTOM START**

- Questioning and documentation of possible occurrence of AEs/device deficiencies
- Questioning and documentation of new or changed concurrent treatment
- Review of the diary by a study team member (except investigator)
- Assessment and documentation of cold
- Checking criteria for further participation
- Physical examination
- Measurement of blood pressure and pulse rate

Between V1 and V2, the study site will have monthly phone contact with the subjects as a reminder about the study.

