- answering "Yes" to either of the questions in the subject diary: "Do you think/feel you have a cold?" or "Do you think/feel you are coming down with a cold (might be having first signs of cold)?"
- Jackson score of at least 1 (mild = sensible, but not disturbing or irritating) for any symptom except headache

Within maximally 3 days after start of the symptoms, the subject should attend the Visit 2 at the investigational site. If the limitation of 3 days may not be held due to e.g. weekend and/or holiday, the Visit 2 could take place on the day following the last non-working day but needs to be clearly documented in the CRF together with an explanation to the delayed visit. During Visit 2, the investigator will perform a physical examination and the study team (not the investigator) will check the subject diaries. The investigator will examine whether the symptoms reported by the subject are still present and if so, whether they are attributable to common cold or the subject suffers from another ailment (e.g. allergy, influenza, sinusitis, pharyngitis, tonsillitis, laryngitis, reflux disease, infectious mononucleosis etc.).

The IP should be used until 2 days after the subject is symptom free (=answering "No" to the question "Do you think that you are still sick with this respiratory infection?" for 2 days in a row), but not longer than 12 days in total.

A common cold episode is defined by the following criteria, which must be met by the subjects at least two days in a row:

- 1) answering "Yes" to the question "Do you think that you are still sick with this respiratory infection?" and
- 2) reporting at least 1 of 4 cold symptoms: nasal discharge (runny nose); nasal obstruction (plugged or congested); sneezing; or sore (scratchy) throat, and
- 3) scoring at least 2 points on the Jackson scale.

Based on the assessment of the symptoms recorded in the diary by means of the above criteria for a common cold episode, as well as the evaluation of any symptoms by the investigator at V2 (whether they are attributable to common cold), the percentage of subjects with prevention of common cold outburst (upon originally having experienced initial symptoms) will be assessed.

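### Ending follow-up when Visit 2 is not held within 3 days of onset contradicts the protocol's own weekend/holiday exception and may lose post-randomisation data selectively

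*Protocol*

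**What the plan says.** All references are to the protocol.

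- **Continuation.** Section 9.3, repeated in the synopsis, says who continues: "Subjects having Visit 2 within maximally 3 days after onset of common cold symptoms according to predefined criteria for required symptoms". In the verum group the sentence also refers to the start of IP use. Section 12.2 puts the rule into practice at V2: "Checking criteria for further participation".
- **Exception.** Section 12.7.1 relaxes the limit: "If the limitation of 3 days may not be held due to e.g. weekend and/or holiday", V2 may be held on the day after the last non-working day, with the reason recorded in the CRF.
- **Numbers.** Section 9.1: "Thereof, the first 200 who attend the V2 should complete the study". The synopsis expects 200 subjects to enter the treatment phase and complete V2 and the study, and 200 to be analysed.
- **Prevention endpoint.** "A common cold episode is defined by the following criteria, which must be met by the subjects at least two days in a row" (Section 12.7.1). Prevention is judged from the diary "as well as the evaluation of any symptoms by the investigator at V2". The investigator checks "whether the symptoms reported by the subject are still present and if so, whether they are attributable to common cold".
- **Analysis population.** The FAS in Section 14.1.3 needs one data point after onset and, in the verum group, one IP dose. V2 is not mentioned.
- **Early exit.** Section 12.10.1 asks early terminators to a final visit equivalent to V3. The flow-chart footnote in Section 21.2 gives them a reduced visit.

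**The concern.** Randomisation takes place at V1 and the verum group starts the IP at onset, so the V2 rule acts after both. Whether a subject comes within 3 days can depend on how the cold is going, which is what the trial measures. Section 10.6 leaves subjects unblinded, so attendance can also depend on arm.

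Read literally, Section 9.3 stops observation of a subject who misses the window. Two things are then exposed. The first is the remaining diary, which carries the symptom scales and the duration of the cold. The second is the blinded V2 evaluation, which feeds the prevention percentage, one of the main endpoints. The stated aim is to compare assessments by the size of the treatment effect each one shows (Section 14.1.1). Missing data that affect one assessment more than another would distort that comparison, even in an exploratory pilot.

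**Working it through.** **1. The passages side by side.** Take a subject whose V2 falls on day 4 because day 3 was a public holiday. Under Section 12.7.1 the visit stands, with documentation. Under Section 9.3 and the synopsis the subject does not meet the condition for continuing. Neither passage refers to the other. This needs no assumption.

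**2. The counts.** The synopsis gives the same figure, 200, for subjects entering treatment, completing V2 and the study, and analysed. That allows for no loss between onset and V2. The FAS would hold those subjects as well. If a share *a* of subjects with onset attends V2, then 200 attenders correspond to 200/*a* subjects with onset:

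- *a* = 0.95 (assumed): 200/0.95 = 211
- *a* = 0.90 (assumed): 200/0.90 = 222

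The synopsis and Section 9.1 also call the 200 the number with symptoms, with a tolerance of 20 either way (180 to 220). The second case falls outside it. The protocol's 200/300 = 66.7% combines having a cold with attending V2, so no attendance rate can be taken from it.

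**3. Which data are at risk.** A subject who is symptom-free from the day after onset can record two consecutive days without illness inside the 3-day window. Such a subject who skips V2 may lose little diary, but does lose the V2 evaluation. A subject with a longer cold who misses V2 loses the later diary days. If mild first signs turn into a full episode after day 3, a diary cut off at day 3 would not show it.

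**4. Possible size, illustration only.** Assume that only V2 attenders were analysed. Let *p* be the true prevention rate, *a_p* the attendance among prevented colds and *a_n* the attendance among the others.

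Observed rate = *p·a_p* / [*p·a_p* + (1 − *p*)·*a_n*]

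Assume *p* = 0.20 (control) and 0.35 (verum), *a_n* = 0.95, and *a_p* equal in both arms. For example, with *a_p* = 0.60:

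- control: 0.12/(0.12 + 0.76) = 0.136
- verum: 0.21/(0.21 + 0.6175) = 0.254

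| *a_p* | control | verum | difference (points, from unrounded rates) |
|---|---|---|---|
| 0.95 | 20.0% | 35.0% | 15.0 |
| 0.80 | 17.4% | 31.2% | 13.8 |
| 0.60 | 13.6% | 25.4% | 11.7 |
| 0.40 | 9.5% | 18.5% | 9.0 |

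**5. Attendance that differs by arm, no true effect.** Set *a_p* = 0.90 in one arm and 0.60 in the other, with *a_n* = 0.95. At *p* = 0.20 the observed rates are 0.18/0.94 = 19.1% and 0.12/0.88 = 13.6%, a false difference of 5.5 points. At *p* = 0.10 it is 3.0 points and at *p* = 0.30 it is 7.6. The sign depends on which arm attends better.

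**The case against.** A reader might infer more: that the prevention endpoint loses its own successes, because quickly resolving colds drop out and are removed from the analysis. The protocol does not support that.

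- The FAS does not require V2, and Section 12.7.1 words the prevention percentage for subjects who had initial symptoms. A subject whose cold clears early has diary data from the first day and (in the verum group, after one dose) stays in the FAS. The attenders-only denominator in steps 4 and 5 is therefore an assumption. The analysed number of 200 is a planning figure and does not define a population.
- Symptoms need not persist at V2. The investigator checks whether they are still present, so a resolved cold is foreseen, and a subject with one who attends continues.
- Early terminators are asked to a final visit. Under either description of it the diary is to be returned, so recorded data are not discarded.
- Lower attendance after quick resolution is plausible, but no figure supports it. Those subjects are still keeping the diary during the V2 window.
- If attendance depends on outcome alone, equally in both arms, each arm's odds are multiplied by the same *a_p/a_n* and the odds ratio is unchanged. In the example it is (0.35/0.65)/(0.20/0.80) = 2.15 before and after. The risk difference shrinks, and no effect is created where none exists.
- How to classify a subject with no V2 could be left to the SAP, which is not at hand.

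All of this stands, and it limits the claim. It does not remove the contradiction over the 3-day limit. Nor does it remove the fact that Section 9.3 decides who remains under observation. An analysis plan cannot recover diary days or a blinded evaluation that were never collected, and the equal-attendance argument is not assured when subjects know their arm.

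**Conclusion.** The point holds in a limited form. Section 9.3 and the synopsis make continued participation depend on a visit that follows randomisation and treatment start. They contradict the weekend/holiday exception in Section 12.7.1. Counting 200 V2 attenders as both completers and the analysed number does not match an FAS that ignores V2.

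Selective loss of later diary data and of the V2 evaluation is possible, but its size and direction cannot be determined from the protocol. The illustrated shrinkage (15 points to between 9.0 and 13.8) and false differences (3.0 to 7.6 points) rest wholly on assumed prevention and attendance rates and on an attenders-only analysis. If prevented and other colds attend equally often, there is no bias in the prevention percentage from this source.

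The study is exploratory with no confirmatory claim, which limits the consequence. The change is still worth making, because prevention is a main endpoint and the correction is cheap.

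**What to change.** 1. Reconcile Section 9.3 and the synopsis with Section 12.7.1 so that V2 timing is not a condition for continued follow-up. Every subject with protocol-defined onset keeps the diary and attends V3. A late or missed V2 is documented as a deviation. This concerns follow-up and data collection only, not IP use.
2. State that the prevention percentage is computed on all FAS subjects with onset, using the diary criteria together with the blinded V2 attribution where it exists, and the diary criteria alone where V2 is missing. Keep the V2 attribution in the main definition: it is the blinded component, and it separates colds from other ailments.
3. Add a sensitivity analysis restricted to subjects with a V2.
4. Report V2 non-attendance after onset by arm.
5. Say in Section 9.1 and the synopsis whether 200 counts subjects with onset, V2 attenders or the FAS, and align the final-visit content in Section 12.10.1 with the flow-chart footnote.

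Cost: protocol wording and a few extra V3 visits. Some subjects will be classified without blinded attribution, on their own unblinded diary. The sensitivity analysis shows how much that matters.
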